## Abstract

**Background:**

Children diagnosed with cerebral palsy (CP) often experience various limitations, particularly in gross motor function and activities of daily living. Transcranial direct current stimulation (tDCS) is a noninvasive brain stimulation technique that has been used to improve movement, gross motor function, and activities of daily living.

**Objective:**

This study aims to evaluate the potential additional effects of physiotherapy combined with tDCS in children with CP in comparison with physiotherapy only.

**Methods:**

This is a 2-arm randomized controlled trial that will compare the effects of tDCS as an adjunctive treatment during rehabilitation sessions to rehabilitation without tDCS. Children with CP classified by the Gross Motor Function Classification System as levels I and II will be randomly assigned to either the sham + rehabilitation group or the tDCS + rehabilitation group. The primary outcome will be the motor skills assessed using the Gross Motor Function Measure domain E scores, and the secondary outcome will be the measurement scores of the children’s quality of life. The intervention will consist of a 10-day stimulation protocol with tDCS spread over 2 weeks, with stimulation or sham tDCS administered for 20 minutes at a frequency of 1 Hz, in combination with physiotherapy. Physical therapy exercises will be conducted in a circuit based on each child’s baseline Gross Motor Function Measure results. The participants’ changes will be evaluated and compared in both groups. Intervenient features will be tested.

**Results:**

Data collection is ongoing and is expected to be completed by January 2025. A homogeneous sample and clear outcomes may be a highlight of this protocol, which may allow us to understand the potential use of tDCS and for whom it should or should not be used.

**Conclusions:**

A study with good evidence and clear outcomes in children with CP might open an avenue for the potential best use of neurostimulation.

**Trial Registration:**

Brazilian Registry of Clinical Trials RBR-104h4s4y; https://tinyurl.com/47r3x2e4

**International Registered Report Identifier (IRRID):**

PRR1-10.2196/52922

## Introduction

Cerebral palsy (CP) is a prevalent cause of physical disability among children, with reported incidence rates ranging from 2.0 to 2.5 per 1000 live births in developed countries, and even higher in low and middle-income countries, reaching up to 7 per 1000 live births [1]. The treatment goals for CP primarily focus on improving motor function and promoting independence in activities of daily living, as well as enhancing quality of life (QoL) [2]. Despite the efforts made in this area, the heterogeneous clinical presentations and responses to interventions pose a challenge in generalizing information about the effectiveness of specific treatment methods [2]. Guidance from the Cochrane Collaboration in 2019 suggests there is a need to standardize the outcomes studied in interventions, to provide functional and informative results and guide the selection of the most effective interventions and an effective individualized treatment [3].

Children with CP have difficulties in balance, motor function, and movement coordination. Physical therapy is used to improve these disabilities. Transcranial direct current stimulation (tDCS) is a complementary intervention that has been shown to enhance balance and improve movement coordination and gross motor function in children with CP [2,4,5]. There is a difference in oscillation speed when associating tDCS with virtual reality [5]. De Almeida Carvalho Duarte et al [2] have shown that children with CP subjected to 5 sessions of treadmill training stimulated with tDCS for 2 weeks with stimulation in M1 for 20 minutes exhibited improvements in temporal functional mobility, such as gait. The results were still maintained 1 month after the intervention. Balance and functional performance seem improved in children with CP after 5 sessions of tDCS anodal stimulation of the motor cortex plus treadmill training for 2 consecutive weeks.

Just 1 session of tDCS realized in the M1 region for 20 minutes in a group of children with CP showed a momentary increase in cortex activation with a direct influence on motor control and an improvement in gait and balanced outcomes [6]. Permanent effects in the population submitted to tDCS with clinical effects were observed in promoting functional improvement in children with CP [2,4].

According to the previous results, we hypothesized that tDCS use might improve specific motor skills and positively impact QoL in a more homogeneous population with CP. This study was designed to examine the impact of the combination of tDCS and conventional rehabilitation exercises on the improvement of gross motor function in children with CP classified as level I and II in the Gross Motor Function Classification System (GMFCS). The primary outcome measure will be assessed using the scores of the Gross Motor Function Measure (GMFM) dimension E and the secondary outcome is the children’s QoL.

According to Castelli and Fazzi [7], rehabilitation is a complex process that aims to promote the best possible participation and QoL for the child and the family. Rehabilitation for children with CP must be timely, intensive, and family-centered [7]. Despite the importance of understanding the effects on children’s QoL, QoL is not commonly measured.

Castelli and Fazzi [7] recommend intensive rehabilitation with trained professionals and a multidisciplinary team focused on the child’s functional improvement. Rehabilitation is one of the main parts as it involves performing functional assessments, establishing a functional prognosis, constructing a rehabilitation plan, and promoting a multidisciplinary approach [7].

## Methods

This study is a single-blind randomized controlled trial (RCT). The participants will be blinded to the treatment allocation during the trial, but the researchers conducting this study will be aware of the treatment allocation. This study will conform to the CONSORT (Consolidated Standards of Reporting Trial) guidelines for nonpharmacological interventions. This study has been approved by the ethics committee in research.

### Recruitment

All patients with CP who meet the previously described criteria for inclusion will be invited to participate in this study which will be realized in the Molecular Medicine Center of the Universidad Federal de Minas Gerais in Brazil.

### Sample Size

The sample size was calculated using G* Power software (version 3.1; Universität Düsseldorf) [8]. Considering an effect size of 0.5, power of 0.95, and probability of type I error (α) of 5%, the total sample size should be 176 volunteers, with 2 groups of 88 volunteers. The impact of the intervention will be evaluated in the pilot phase to determine a more accurate estimate of the population sample size. The participants will be included from July 2023 to July 2024. After the end of the intervention, the data collected will be separated into groups, these being the intervention group (IG) and the control group (CG). We will carry out the analysis of the pre- and postintervention GMFM variables and the Pediatric Quality of Life Inventory (PedsQL). We will carry out the analysis between groups (CG and IG) and between individuals in the same group, and will compare participants with themselves, to quantify and describe the results. Analysis of covariance will be chosen to observe preexisting differences between groups, allowing for comparison of postintervention scores while controlling for baseline scores.

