#### Adverse Effects

Adverse effects will be assessed using the tDCS adverse effects questionnaire [16]. The dropout rate will be reported, and dropout reasons will be stated [15]. tDCS is generally well-tolerated with no serious adverse events [14]. The effects reported are rare, mild, and transient, with “redness,” “slight tingling,” “itching,” and “burning sensation” as the most reported events. The intensity of current, density, and electrode size will be optimized to modulate the tingling and itch perception during transcranial stimulation. Furthermore, we will not pass the well-accepted threshold of tDCS current density (<142.9 A/m^2^ or 14.29 mA/cm^2^) [14].

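### The 176-child sample size matches the stated inputs only as a one-sided t-test that is never declared; a two-sided 5% test without baseline adjustment has about 91% power, not 95%

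*Protocol article*

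**What the plan says.** The Sample Size section gives the calculation in one sentence. It begins "Considering an effect size of 0.5", continues "power of 0.95, and probability of type I error (α) of 5%, the total sample size should be 176 volunteers", and divides these into two groups of 88. G*Power 3.1 is named as the software. The section names no test family, no effect-size metric and no sidedness.

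The next sentence says that the pilot phase will be used to refine the sample size, so 176 is provisional.

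For the between-group comparison the same section says "Analysis of covariance will be chosen to observe preexisting differences between groups", with post-intervention scores compared while controlling for baseline. No baseline-to-post correlation is given there or elsewhere. The Allocation section sets a 1:1 ratio. The Introduction words the hypothesis in one direction: "we hypothesized that tDCS use might improve specific motor skills".

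**The concern.** A reader who meets a 5% type I error with no further qualification will normally take it as two-sided, and the group effect in a covariance analysis is conventionally tested that way. On that reading, the stated effect size, power and sample size do not fit together.

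Two things depend on it. The first is the stated power: 95% would be quoted as a property of the design when an unadjusted two-sided test at the same inputs falls about 4 percentage points short. The second is the error rate. If the 95% were kept by testing one-sided at 5%, the chance of wrongly declaring benefit would be 5%, against 5%/2 = 2.5% in the favourable direction under a two-sided 5% test. That is a design choice which the protocol would have to state openly.

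**Working it through.** **Inputs.** Effect size 0.5, power 0.95, α = 0.05 and n = 88 per group come from Sample Size; 1:1 allocation comes from Allocation. The metric of the effect size is not named. It is read here as Cohen's d, a difference in means divided by the standard deviation.

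**Formula.** For two groups of n, the t statistic has 2n − 2 degrees of freedom and noncentrality δ = d·√(n/2). Power is the probability that a noncentral t variable exceeds the critical value: the upper 5% point if one-sided, the upper 2.5% point if two-sided (plus a negligible lower tail).

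**Reproducing the stated figure (one-sided 5%).**
- n = 87: δ = 0.5·√43.5 = 3.298, critical value 1.654 on 172 df, power 0.9495.
- n = 88: δ = 0.5·√44 = 3.317, critical value 1.654 on 174 df, power 0.9514.

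So 88 is the first n to reach 0.95, and 2 × 88 = 176. The match is exact.

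**The same inputs, two-sided 5%.**
- n = 88: δ = 3.317, critical value 1.974, power 0.910. The type II error is 9%, not 5%.
- n = 104: power 0.9483. n = 105: power 0.9501. So 105 per group are needed, 210 in total.
- The effect detectable with 95% power at 88 per group is d = 0.546.

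The normal approximation agrees closely: 87 per group one-sided, 104 per group two-sided, and two-sided power of 0.913 at 88.

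**Other tests at the stated inputs.**

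| Test | Total for 95% power |
|---|---|
| Wilcoxon–Mann–Whitney, normal data, one-sided | 184 |
| Wilcoxon–Mann–Whitney, normal data, two-sided | 220 |
| F test, f = 0.5 | 54 to 55 |
| F test, f = 0.25 (equivalent to d = 0.5 with two groups) | 210 |

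None gives 176. Methods that take a correlation as an extra input, such as covariance or repeated-measures analysis, can be brought near 176 by choosing that correlation, but the protocol states none.

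**Credit for baseline adjustment.** If d = 0.5 is on the unadjusted standard deviation and r is the baseline-to-post correlation, adjustment raises the effective effect size to 0.5/√(1 − r²). For example, r = 0.5 gives 0.5/√0.75 = 0.577. The documents give no value of r, so a range is shown, two-sided at 5%, with 88 per group:

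| r (assumed) | Power |
|---|---|
| 0 | 0.910 |
| 0.3 | 0.933 |
| 0.4 | 0.949 |
| 0.5 | 0.968 |
| 0.6 | 0.985 |

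Power reaches 0.95 just above r = 0.40; at r = 0.41 it is 0.951.

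**Illustration only: fewer children analysed.** With an assumed 10% loss (0.9 × 88 ≈ 79 per group), two-sided power is 0.878 unadjusted and 0.950 at r = 0.5.

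**The case against.** The strongest reply is that nothing has been miscalculated. The protocol does not say two-sided, its hypothesis is worded as an improvement, and 176 is exact for a one-sided 5% test. That stands in part: the fault is an undeclared choice, and 176 is right if a one-sided test was intended. But a directional hypothesis is not a declaration of a one-sided test, and no section makes one. The sentence needs correcting on either reading.

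A second reply is that the planned analysis is not an unadjusted t-test. This also stands. If d is on the unadjusted standard deviation, 0.910 is a lower bound for the planned covariance analysis, and a moderate correlation restores 95%. It does not explain the stated figure, because no correlation is given and the match to the one-sided t-test is exact without one.

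Third, the sample size is provisional pending the pilot phase. That is so, but a later refinement does not correct the present statement.

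Two stronger inferences should not be drawn:

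- A reader might take the Abstract's interest in "for whom it should or should not be used" as proof that a two-sided test is intended. The phrase concerns which children may benefit; it is silent on sidedness.
- A reader might infer that the protocol expects dropout and failed to allow for it. The Adverse Effects section says only "The dropout rate will be reported, and dropout reasons will be stated". It gives no rate, and an allowance may sit in the full protocol that the article condenses.

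**Conclusion.** The point holds as a correction to a stated design figure. At the stated inputs, 176 is the one-sided t-test answer, and the protocol declares no such test. Under a two-sided 5% test without baseline adjustment, power at 88 per group is about 91% rather than 95%, a shortfall of about 4 percentage points. This rests on reading the effect size as Cohen's d, which the exact match supports, and on all 88 per group being analysed.

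A reader might go further and conclude that the trial is underpowered or must enrol 210 children. The documents do not support that. Power of 91% is still high, and the planned adjustment could bring it to 95% or above at a correlation that the protocol does not state. The correction is worth making but is not a condition for the trial to proceed.

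**What to change.** In Sample Size, state that the primary between-group test is two-sided at 5%, and then do one of the following:

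1. Restate the power: 88 per group analysed gives about 91% power for d = 0.5 (two-sided two-sample t-test).
2. Base the calculation on the planned covariance analysis. State the assumed baseline-to-post correlation and that d is on the unadjusted standard deviation. A correlation of about 0.41 or more supports 95% with 88 per group; 0.5 gives 0.968.

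In either case, name the test and the effect-size metric, and make clear that the power refers to the number analysed. If a one-sided 5% test was truly intended, the protocol must say so and justify it.

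The cost is a sentence or two and, under the first option, a slightly less favourable stated power. No extra enrolment is needed.

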### Allocation

Participants will be randomly assigned to tDCS groups with a 1:1 allocation as per a computer-generated randomization schedule stratified by the patient’s age using 5 permuted blocks of 6 participants.

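### The sample size is to be revised from the treatment effect seen in a pilot phase, which is too imprecise for that: a separate pilot costs power, and unadjusted pooling inflates type I error

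*Protocol article*

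**What the plan says.** The Sample Size section of the protocol article sets the planning values: "Considering an effect size of 0.5", power of 0.95 and a "probability of type I error (α) of 5"%. It concludes that "the total sample size should be 176 volunteers, with 2 groups of 88 volunteers". The next sentence makes that total provisional: "The impact of the intervention will be evaluated in the pilot phase to determine a more accurate estimate of the population sample size".

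The final comparison is an analysis of covariance, "allowing for comparison of postintervention scores while controlling for baseline scores". The Allocation section randomises children "with a 1:1 allocation as per a computer-generated randomization schedule". Neither these sections nor any other part of the article limits the revision or says that it rests on anything other than the intervention's effect.

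**The concern.** The quantity to be evaluated in the pilot is the impact of the intervention, which is the between-arm effect and not a nuisance parameter such as the SD. The article presents the resulting sample size as an improvement on the planned one. A target effect is a fixed choice and carries no sampling error. A pilot estimate carries a great deal, and because the required number varies with 1/d², that error is magnified.

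Either the power claim or the type I error is at stake, depending on how pilot children are used. A between-arm pilot result also requires allocation and outcome to be linked. The Blinding section gives the randomisation results only to the neuromodulation member and the scale results only to the assessor, and names no one who may hold both.

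**Working it through.** **Inputs.** From the Sample Size and Allocation sections: d = 0.5, power 0.95, α = 0.05 (sidedness not stated), 1:1 allocation, 88 per group. Assumptions not in the document: a pilot of 10 to 30 per arm, a cap of 300 per arm (also used when the pilot effect is zero or negative), normal data and a two-sample t-test.

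**Step 1. The plan's own figure.** n per arm = 2 × ((z_α + z_β)/d)².
- One-sided: 2 × ((1.645 + 1.645)/0.5)² = 86.6, so 87. The exact noncentral t gives 88, a total of 176, which matches.
- Two-sided: 2 × ((1.960 + 1.645)/0.5)² = 104.0, so 104. The exact value is 105, a total of 210.

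Only a one-sided test reproduces 176, so both bases are shown below.

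**Step 2. Precision of a pilot effect.** SE(d) = √(2/m + d²/(4m)) for m per arm, at d = 0.5:
- m = 10: √(0.2000 + 0.0063) = 0.454, half-width 1.96 × 0.454 = 0.89
- m = 20: √(0.1000 + 0.0031) = 0.321, half-width 0.63
- m = 30: √(0.0667 + 0.0021) = 0.262, half-width 0.51

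**Step 3. What the noise does to n.** Take the one-sided formula and suppose that the true d is 0.5.
- An observed d of 0.8 gives 2 × (3.29/0.8)² = 33.8, so 34 per arm. Power by the normal approximation is Φ(0.5 × √(34/2) − 1.645) = Φ(0.417) = 0.66.
- An observed d of 1.0 gives 22 per arm, with power Φ(0.013) = 0.51.

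On the one-sided basis about half of pilots would cut n below 88. The pilot effect is zero or negative in about 13%, 6% and 3% of pilots of 10, 20 and 30 per arm.

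**Step 4. Average consequences.** Simulation, 400,000 runs per setting. The power columns use a true d of 0.5, and the type I column uses d = 0.

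| Pilot per arm | Test | Separate: average power | Separate: share with true power < 80% | Pooled: average power | Pooled: type I error |
|---|---|---|---|---|---|
| 10 | one-sided | 81% | 37% | 93% | 7.0% |
| 10 | two-sided | 79% | 39% | 90% | 6.0% |
| 20 | one-sided | 85% | 32% | 98% | 6.6% |
| 20 | two-sided | 83% | 34% | 96% | 5.8% |
| 30 | one-sided | 87% | 28% | 99% | 6.3% |
| 30 | two-sided | 86% | 30% | 98% | 5.7% |

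With a separate pilot, type I error stays at 5%. Pooling largely keeps power because a small revised trial follows a pilot that already showed a large effect, and that effect is carried into the final test. The same mechanism inflates type I error. Changing the cap to 176 or 500 per arm hardly alters the separate-pilot power. The one-sided pooled type I error is then 5.9-6.7% (cap 176) or 6.6-7.1% (cap 500).

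**Step 5. The alternative.** If n is revised only from the pilot SD against a fixed difference, with pilot children pooled (10 to 30 per arm), type I error is 5.0-5.2% and power 92-94%. Keeping 88 per arm at d = 0.5 gives power of 95.1% one-sided or 91.0% two-sided.

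**The case against.** The strongest reply is that the article is a condensed account. Pilot size, limits on the total, the handling of pilot children and the protection of type I error may all be set out in the full protocol or analysis plan. That stands: their absence is not the finding. The finding is the stated rule, that the observed effect will set the sample size and make it more accurate.

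A second reply is that 0.5 is itself unsourced, so pilot data might improve on it. The lack of a source is a reason to justify the target difference, not to replace it with an estimate whose error is as large as the target.

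A reader might infer that, whatever is done with the pilot, the 95% power is lost and there is an uncontrolled interim look. The document does not support that, because it merges two incompatible readings. With a separate pilot there is no look within the confirmatory data and type I error is intact. With a pooled pilot average power is largely kept. Low fixed-design powers, such as the 66% above, apply only to a separate pilot.

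Two other inferences also fail. The Allocation section's five blocks of six describe the trial's randomisation and say nothing about pilot size. And no stated ceiling on recruitment shows that an upward revision would be unachievable.

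**Conclusion.** The concern holds in conditional form. Revising the total from an observed pilot effect is a poor stated rule, because at 10 to 30 per arm the estimate's 95% half-width (about 0.9 to 0.5) equals or exceeds the planned effect. A separate pilot reduces average power from the stated 95% to about 79-87% and leaves true power below 80% in about 28-39% of cases. Unadjusted pooling keeps average power at about 90-99% but raises type I error to about 6-7% and makes the pilot an unblinded interim look. The two harms do not occur together.

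The sizes rest on assumed pilot numbers, an assumed cap and a true d of 0.5. The calculation uses a t-test; baseline adjustment changes the scale of n but does not remove the noise in the pilot effect. The point should be corrected, with medium confidence in the exact sizes and more in the direction.

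**What to change.** Replace the pilot sentence with:

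> The target effect stays at 0.5 SD and the planned total is not reduced on the basis of an observed treatment effect. The pilot phase is used, blinded and pooled over arms, only to re-estimate the SD of GMFM-E and its baseline-post correlation for the ANCOVA. No between-arm effect is computed before the final analysis.

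The target should also be given in GMFM-E points with a justification. If it is fixed only in SD units, a new SD estimate cannot change the sample size. A blinded variance lumps the arms and is inflated by 1 + d²/4 = 1.0625 at d = 0.5, so n would be about 6% larger, which is a mild and safe error. Keeping 176 as a minimum would add protection.

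If a between-arm pilot effect has already been seen and used to set the sample size, either exclude those children from the confirmatory analysis or use a method that controls type I error.

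The cost is mainly wording and the loss of an early indication of effect size. The article describes data collection as ongoing, so the change may also cost pilot children already looked at: 20 to 60 in total for pilots of 10 to 30 per arm.

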### Measures

#### Overview

Both instruments will be used with all participants before and after the interventions to assess whether there was a significant improvement in gross motor movement according to the E domain of the GMFM or in QoL.

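### The stated ANCOVA does not name the age factor used to stratify randomisation, and a before/after improvement criterion stands beside it that can be met without any tDCS effect

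*Protocol article*

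**What the plan says.** - **Randomisation.** Allocation is 1:1, "as per a computer-generated randomization schedule stratified by" age (Allocation). Age cut-points are not given; eligible children are 8 to 12 years old.
- **Model.** The analysis text, which sits under Sample Size, names an ANCOVA "allowing for comparison of postintervention scores while controlling for baseline scores". Baseline score is the only covariate mentioned.
- **Within-arm comparisons.** The same paragraph plans an analysis between the groups and also "between individuals in the same group, and will compare participants with themselves", with a stated purpose of quantifying and describing the results.
- **Improvement criterion.** The Measures overview has every child complete both instruments at the start and again once treatment ends. The aim it gives is "to assess whether there was a significant improvement in gross motor movement according to the E domain of the GMFM or in QoL".
- **Question and outcomes.** The Abstract's objective is the effect of tDCS added to physiotherapy, compared with physiotherapy only. GMFM dimension E is primary and quality of life is secondary.
- **Control.** The sham arm receives ten rehabilitation sessions over two weeks, as the tDCS arm does (tDCS Intervention; Interventions: Participants).
- **Sample size.** The inputs are given as "Considering an effect size of 0.5, power of 0.95, and probability of type I error (α) of 5" percent. The result stated from them is that "the total sample size should be 176 volunteers, with 2 groups of 88 volunteers".

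**The concern.** There are two separate issues.

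First, stratifying by age removes chance age imbalance from the treatment contrast. A model without age leaves the age-related variance in its residual, so its standard error does not reflect that balance and is too large. At stake is some precision, not a false-positive risk.

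Second, the trial asks a between-arm question, but the Measures overview describes a before/after significance finding with no comparator. Children in both arms train towards GMFM-E for ten sessions, so a pre-post gain is plausible in each arm with no contribution from tDCS. If one arm's pre-post result crosses the 5% line and the other's does not, the text allows that to be reported as an improvement. This second issue could change what the trial is said to have shown.

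**Working it through.** **1. The plan's own figure.** Inputs from Sample Size: effect size 0.5 (taken as a standardised mean difference; the metric is not named), power 0.95, α 5% (sidedness not stated), 88 per arm. With a two-sample t-test the noncentrality is 0.5 × √(88/2) = 3.317.
- One-sided 5%: power at 88 per arm is 0.951, which reproduces 176.
- Two-sided 5%: power at 88 per arm is 0.910; 105 per arm (210) would be needed for 0.95.

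The undeclared sidedness is a separate matter. The power figures below are two-sided, starting from 0.910.

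**2. Leaving age out.** Let R² be the share of the variance remaining after baseline that age explains. The documents give no value, so 1% to 10% is an assumption.
- SE overstatement = 1/√(1 − R²)
- Type I error without age = 2 × [1 − Φ(1.96/√(1 − R²))]
- Power with age: noncentral t with noncentrality 3.317/√(1 − R²)

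| Assumed R² | SE too large by | Two-sided type I error without age | Power with age (reference 0.910) |
|---|---|---|---|
| 1% | 0.5% | 4.9% | 0.912 |
| 5% | 2.6% | 4.4% | 0.923 |
| 10% | 5.4% | 3.9% | 0.935 |

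The unrounded powers are 0.9096, 0.9123, 0.9228 and 0.9353, so the differences are 0.3, 1.3 and 2.6 points. These are upper figures: the 0.910 reference gives the baseline-only model no credit for the balance that stratification delivers.

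A simulation that does give that credit (176 children, five assumed age strata, permuted blocks of 6; 10,000 null and 5,000 alternative runs) found:
- R² = 4%: power 0.914 without age and 0.918 with it; type I error without age 0.043.
- R² = 9%: power 0.917 without age and 0.931 with it; type I error without age 0.040.

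The direction is the same, with gaps of 0.4 and 1.4 points.

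**3. Pre-post significance with no tDCS effect.** Inputs: 88 per arm, paired t-test, two-sided 5%, 87 degrees of freedom (critical value 1.988). Both arms have the same true gain g, in SDs of the change score. The documents give no expected gain, so a range is shown.
- p = P(an arm shows significant improvement), from a noncentral t with noncentrality g × √88
- P(tDCS arm significant, sham arm not) = p × (1 − p), because the arms are independent

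| Assumed gain g | g × √88 | p | p × (1 − p) |
|---|---|---|---|
| 0.1 | 0.94 | 0.151 | 0.128 |
| 0.2 | 1.88 | 0.458 | 0.248 |
| 0.3 | 2.81 | 0.795 | 0.163 |
| 0.5 | 4.69 | 0.996 | 0.004 |

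A valid two-sided 5% between-arm test would favour tDCS wrongly in 2.5% of trials. The last column falls at large gains only because both arms are then nearly always significant. The p column shows that the tDCS arm viewed alone would then look improved 99.6% of the time.

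**The case against.** **On age.** The article does not say that baseline is the only covariate. It is a condensed account, the Abstract says that intervening features will be tested, and a full covariate list commonly belongs in an analysis plan that is not shown. The loss is small, depends on an assumed R² within a narrow age range, and errs on the safe side. All of this stands. A reader might infer that age has been excluded from the analysis, or that the ANCOVA is invalid; the documents support neither. What remains is that the one model described does not include the one factor randomisation uses.

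**On within-arm comparisons.** Sample Size gives them a descriptive purpose, names no within-arm test, and names ANCOVA as the only method; the objective is between-group. That also stands, so the article cannot be read as making within-arm tests its stated evidence. But the descriptive phrase covers the between-group analysis too, so it does not set the within-arm part apart, and the Measures overview asks for significance with no mention of the control arm.

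**On size.** A reader might count every trial in which exactly one arm is significant. That doubles the figures by including sham-only significance, which could not support a claim for tDCS, so only one direction is counted here.

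**On "to assess whether there was a significant improvement in gross motor movement according to the E domain of the GMFM or in QoL".** The word joining the two outcomes might be read as a rule that either one suffices, with the inflated error that follows. The Abstract, Introduction and Discussion all rank GMFM-E first and quality of life second, so that reading is not supported.

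**On GMFCS level.** It is an eligibility criterion and not a randomisation factor. Adjusting for it is a preference, and its absence is not a fault.

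**Conclusion.** The point holds in a limited form. The age issue is a modest inefficiency: a standard error about 0.5% to 5% too large and at most about 0.3 to 2.6 points of two-sided power, if age explains 1% to 10% of the variance left after baseline. Type I error is not inflated.

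The before/after wording matters more. With no tDCS effect, reading significance arm by arm would favour tDCS in about 13%, 25% or 16% of trials at equal gains of 0.1, 0.2 or 0.3 SD of change, falling to 0.4% at 0.5 SD. These figures depend on the assumed gains and on someone using the arm-by-arm reading; the article permits that reading but does not prescribe it. Nowhere does it say which comparison decides the trial. Both parts should be corrected before analysis; neither undermines the design.

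**What to change.** - State that the between-arm ANCOVA of post-treatment GMFM-E, adjusted for baseline GMFM-E and age stratum (or age in years), is the only test that decides the trial.
- Use the same model for PedsQL, with its own baseline score, as the secondary outcome.
- Report within-arm changes as means with confidence intervals, without tests.
- Reword the Measures overview so that it refers to a difference between the groups after treatment instead of a before/after improvement.

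This needs no extra data or participants. It costs a few sentences of wording and a few degrees of freedom: four if age enters as five strata, one if it enters in years. The sample size of 176 need not change on this account.
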